### Recruitment

Participants will be referred to the study via several pathways that have been developed in collaboration with community partners, including PCPs, PASS clinicians, and parents. Clinicians in primary care, including PCPs and behavioral health clinicians, can refer potentially eligible patients to our team through the EHR. The referring clinician will inform the family about the study and, with parent permission, indicate in the EHR that the family has agreed to be contacted by the study team. Another pathway is through automated review and reporting from the EHR. Specifically, children who receive care in one of the participating practices may be identified as potential participants if their EHR indicates that they meet preliminary inclusion criteria (i.e., documented ADHD diagnosis, between 5 and 11 years old, evidence of low-income status in the EHR). Reports will be generated regularly and provided to the study team. Then the study team will reach out to the associated PCP and inquire about the suitability of the family for the study. As an additional recruitment tool, the study team has created recruitment letters and cards with a QR code that enables families to express interest in the study directly with study team members. If the family is interested, the family will complete an online questionnaire that will capture contact information. Completion of the survey will act as confirmation of willingness to be contacted by the study team to gauge interest and complete a phone screen.

Regardless of referral pathway, the study team will contact families by telephone to screen them for the study and, if potentially eligible, obtain their verbal consent to advance through the recruitment process. The screening will include requesting parents to respond to questions to verify that inclusion criteria are met and determine whether exclusion criteria are present. If families are eligible and provide verbal consent, they will be scheduled for a study visit to obtain written consent and collect baseline data. During the initial phone contact, families will be given the option to participate in the study or decline participation. If families decide not to participate, they can be referred either to the integrated behavioral health provider within their primary care practice, including brief behavior therapy with limited school collaboration and no support from a Community Health Partner, or to a community-based behavioral health provider.

If families participate in the study, they will be randomly assigned to PASS or TAU. With family consent, a member of the research team will contact the child’s teacher. We will use procedures successfully employed in previous studies [41] to obtain teacher buy-in: (a) an email will be sent to inform the principal that a parent or guardian has given permission for data collection from a student’s teacher, and the principal will be encouraged to contact the team if there are any concerns, (b) a member of the team will contact the teacher via phone and email, (c) teachers will be provided a “Teacher Information Sheet” that includes details of the study and a copy of the signed consent form giving parent permission to obtain data from the teacher, and (d) the study team will ask the teacher to complete baseline measures and a brief demographic form. Similar procedures will be used for data collection at other assessment points. See Fig. 2 for an illustration of participant flow through the study.

**Fig. 2 Fig2:**
[figure not shown]
PASS Study Participant Flow CONSORT

### Assignment of interventions

Participants will be randomly assigned to condition at a 1:1 ratio. Randomization will be stratified by child medication status (on or off ADHD medication at the time of consent) and practice site (seven practices).

#### Sequence generation

The sequence of assignments to treatment conditions will be generated using a computerized randomization algorithm, ensuring an unbiased and unpredictable assignment of participants to the study arms. The randomization list will be securely uploaded into REDCap (Research Electronic Data Capture) [61, 62].

#### Allocation concealment mechanism

Randomization will occur after informed consent is obtained from parents/legal guardians and assent is obtained from children (if indicated). We will use the randomization module in REDCap, so there will be no opportunity for study team members to become aware of group allocation until the computer reveals the result. A study statistician will generate the allocation table using statistical software and upload the table into REDCap without sharing the table with any research team members.

#### Implementation

Randomization procedures including allocation sequence will be generated by a study statistician. For each participant, the allocation will be revealed at the time of enrollment. A study team member will inform parents/legal guardians and children about treatment assignment after obtaining consent and assent (if indicated).

#### Concealment

Given that the study is a pragmatic trial being conducted under real-world conditions, no attempt will be made to conceal treatment assignment condition from parents/legal guardians and children. In addition, no attempt will be made to conceal treatment assignment from study team members, PCPs, behavioral health clinicians, and teachers.

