#### Data collection and management

Data collection strategies were designed in partnership with caregiver, educator, and clinician partners. The strategies will be reviewed and modified throughout the study to maximize participant engagement in data collection and minimize missing data. Baseline data will be collected from parents and children at the time of consent, and baseline data will be collected from teachers shortly thereafter. Mid-treatment data (specifically the ODD items from the Vanderbilt scale and the Inattention/Task Avoidance items of the Homework Problem Checklist) will be collected from parents approximately 8 weeks after baseline, and post-treatment data will be collected from parents and teachers 16 weeks after baseline. Follow-up data will be collected from parents and teachers 32 weeks after baseline. Study data will be collected and managed using REDCap tools hosted at our institution [61, 62].

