#### Plans to address missing data

Numerous strategies will be applied to minimize missing data, including persistent efforts to contact parents and teachers, disseminating study newsletters on a periodic basis, and motivational interviewing strategies. Alternative methods of imputation, including the maximum likelihood method [63] and multiple imputation method will be considered. In addition, we will check whether patterns of missingness differ between the PASS and TAU groups to determine whether the amount of missingness is associated with a particular group.

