## A priori plans for data analysis for each objective

### Objective 1 (Evaluate differences between PASS and TAU in improving service utilization and child health outcomes)

To evaluate changes in service utilization, we will examine between-group changes in the proportion of children receiving mental health services (i.e., outpatient mental health therapy, school mental health services and special education services, and psychotropic medication) from pre-treatment to post-treatment to follow-up using the McNemar test. To evaluate the effect of intervention on child outcomes, a mixed effects model with repeated measures (MMRM) will be the general analytical approach employed. The model will examine intervention effects across four time points (baseline, mid-treatment [parent report of homework performance and behavior compliance only], post-treatment, follow-up). Data for all participants randomized to treatment condition will be included in the analytic model, consistent with an intent-to-treat (ITT) approach. Mixed effects models will estimate within-subject effects by time and between-treatment effects, as well as the interaction of time by treatment. A significant time by treatment interaction will indicate that one treatment is superior to the other. MMRM will include the fixed categorical effects of treatment, time, randomization stratification factor (medication status and primary care practice), and treatment-by-time interaction as well as covariates as indicated. Within-participant error variance–covariance will be assumed to be an unstructured matrix. Point estimates and confidence intervals for the mean change in outcomes for each treatment group as well as the difference in the estimated mean change between groups will be calculated.

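### Assignment is left open to the whole study team, with no exception for analysts or follow-up staff and no reason specific to them; masking the analyst and using one contact schedule would be cheap safeguards

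*Protocol article*

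**What the plan says.** The Concealment section has two parts. The first gives a reason and applies it to families, that is, caregivers and the child: "Given that the study is a pragmatic trial being conducted under real-world conditions, no attempt will be made to conceal treatment assignment condition from parents/legal". The second adds, with no further reason, that "no attempt will be made to conceal treatment assignment from study team members, PCPs, behavioral health clinicians, and teachers". Statisticians and follow-up staff are not named separately, and no masked assessor or masked analyst is described elsewhere in the article. Allocation concealment mechanism protects the sequence only up to the moment REDCap reveals the assignment.

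On follow-up, Plans to address missing data lists "persistent efforts to contact parents and teachers, disseminating study newsletters on a periodic basis, and motivational interviewing strategies". Data collection and management adds: "The strategies will be reviewed and modified throughout the study to maximize participant engagement in data collection and minimize missing data".

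On analysis, the Objective 1 plan fixes the core of the mixed model (treatment, time, stratification factors, treatment-by-time interaction, unstructured covariance) and then allows for more: "as well as covariates as indicated". On missing data it says: "Alternative methods of imputation, including the maximum likelihood method [63] and multiple imputation method will be considered".

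**The concern.** Families, primary care providers and behavioral health clinicians cannot sensibly be masked in a trial of this kind, and the pragmatic setting explains that. Research staff who send reminders and statisticians who fit models are not part of routine care, so the same explanation does not reach them. The decision to leave them unmasked is stated outright, which makes it a rule of the plan and not merely a detail the article left out.

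Two things are at stake. Staff who know the arm, and who may decide how hard to pursue each family, could obtain outcomes more completely in one arm than in the other. Analysts who know the arm could be influenced, even without intent, when they settle any choices still open. Both primary outcomes are rated by parents who know their arm, and the design cannot remove that. It is therefore worth closing the routes that it can close.

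**Working it through.** No stated figure in the plan depends on masking, so there is none to reproduce. The check sets the sections side by side.

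1. **Who is unmasked.** Concealment covers study team members without exception. That this includes the statisticians is a fair inference, not a statement.

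2. **Is a reason given for them?** The pragmatic rationale is attached to the sentence on families. The sentence on the study team carries none of its own.

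3. **How much room is there for unequal pursuit?** The Sample size section gives 300 enrolled and 20% attrition:
   - 300 × (1 − 0.20) = 240, which matches the stated number with baseline and at least one other assessment.
   - 300 − 240 = 60 families expected to contribute no usable follow-up.
   - At any single visit the number missing would be at least about 60, because some of the 240 will miss one visit or more.
   - The effort spent on these families is at staff discretion, and the strategies may change during the trial.

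4. **Would the plan catch it?** Plans to address missing data commits to comparing patterns of missingness between PASS and TAU. That can reveal an imbalance once it has happened, but does not prevent one.

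5. **Can unmasked covariate choice move the main test?** Under the Objective 1 model, baseline is one of the response times. Write the mean for child i at time t as μ_t + δ_t·Z_i + γ·X_i, where Z is arm and X is a baseline covariate entered as a main effect. The change from baseline to time t then has mean (μ_t − μ_0) + (δ_t − δ_0)·Z_i. The term γ·X_i has dropped out. With complete data, adding or removing such a covariate leaves the treatment-by-time contrast where it was. With missing data the cancellation is no longer exact, but the leverage is small. Covariates that interact with time, or that vary over time, would behave differently; the article does not say that any are intended.

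6. **Is masking feasible?** For analysts, yes: Data monitoring refers to project statisticians in the plural, so someone other than the author of the allocation table appears to be available. For callers, only in part: Implementation has a team member tell families their arm, the notes to Table 2 show at least one measure given only in PASS, and Trial design has parents in both arms report the services they receive.

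**The case against.** The strongest reply has four parts.

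- **The open choices belong in an analysis plan.** This is right. Covariates and the imputation method are commonly left to a statistical analysis plan, which is not shown and may fix them before arm-level data are seen. Their openness in the article is therefore no fault in itself. What remains is that nothing shown masks the analyst while such choices are made.
- **No one is said to choose with the arm known.** Also right; it is a possibility that the stated rule leaves open, not something the plan describes.
- **The planned analysis blunts both routes.** A reader might infer that picking covariates with the arm known would materially inflate the type I error. The documents do not support that, because a main-effect covariate essentially cancels from the treatment-by-time contrast. A reader might also try to size the harm as a shift in a complete-case mean under unequal response. That is not the planned estimator: the mixed model keeps all randomised participants and uses each available assessment. Unequal pursuit biases it only so far as missingness depends on outcomes that the observed data do not explain. The direction is not fixed either; losing worse-off TAU families would flatter TAU.
- **Masking data collectors is not free, and leaves the main bias in place.** Both parts stand. Families and PASS-only measures can reveal the arm. PASS families also have continuing phone contact with a Community Health Partner, which may affect retention whatever the research staff know. Staff do not rate the primary outcomes; unmasked parents do.

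None of this answers the remaining point: no reason is given for leaving the analyst unmasked or for not standardising contact, and both are easily done.

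**Conclusion.** The concern holds in a limited form. The plan leaves all study team members unmasked, with no exception for analysts or follow-up staff and no reason specific to them. Discretionary follow-up with about 60 of 300 families expected to be lost leaves room for unequal pursuit, which the plan would notice only after the fact. Analysts who know the arm could be influenced on any choices not yet fixed.

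No size can be attached. The documents give no input for either effect, and the mixed model limits both. Sample size, alpha and stated power are unaffected. The conclusion assumes that the statisticians count as study team members and that no unseen document already masks them or locks the analysis. It is a worthwhile, inexpensive improvement. The documents do not support the stronger readings that the trial's error rate is compromised, that the pragmatic label was expressly used to justify unmasked staff, or that all staff could be masked without cost.

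**What to change.** Amend the Concealment section in two respects.

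1. **Analyst.** The analysing statistician, who is not the one who generated the allocation table, works with dummy arm codes until the Objective 1 and 2 models, covariates and missing-data method are locked. PASS-only variables, such as satisfaction with PASS, stay out of the masked dataset. The check of missingness by arm can be run on the dummy codes. If an analysis plan already locks these choices, a sentence saying so and naming who is masked is enough.
2. **Follow-up contact.** Outcome invitations and reminders follow one REDCap schedule with the same contact limit in both arms, and any change of strategy during the trial applies to both arms at once. The arm field is hidden from callers where existing staff make that feasible. This equalises planned research contact even when a caller learns the arm.

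Families, primary care providers, behavioral health clinicians and teachers stay unmasked as planned.

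The cost is a paragraph of text, a change of REDCap user rights and a separation of roles between statisticians. Masking of callers will be incomplete, a contact limit may lose a few responses, and bias from unmasked parent ratings is not removed.

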#### Data collection and management

Data collection strategies were designed in partnership with caregiver, educator, and clinician partners. The strategies will be reviewed and modified throughout the study to maximize participant engagement in data collection and minimize missing data. Baseline data will be collected from parents and children at the time of consent, and baseline data will be collected from teachers shortly thereafter. Mid-treatment data (specifically the ODD items from the Vanderbilt scale and the Inattention/Task Avoidance items of the Homework Problem Checklist) will be collected from parents approximately 8 weeks after baseline, and post-treatment data will be collected from parents and teachers 16 weeks after baseline. Follow-up data will be collected from parents and teachers 32 weeks after baseline. Study data will be collected and managed using REDCap tools hosted at our institution [61, 62].

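### Teacher baseline ratings appear to be taken after the arm is disclosed, yet they anchor the teacher-report change scores and effect sizes

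*Protocol article*

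**What the plan says.** All references are to the protocol article.

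- **Randomisation and disclosure.** Allocation concealment mechanism: "Randomization will occur after informed consent is obtained from parents/legal guardians", with child assent where needed. Implementation: "For each participant, the allocation will be revealed at the time of enrollment". The same section has a team member tell parents and children their arm once consent and assent are in hand.
- **Parent and child baseline.** Data collection and management: "Baseline data will be collected from parents and children at the time of consent". Recruitment describes one visit for both: "they will be scheduled for a study visit to obtain written consent and collect baseline data".
- **Teacher baseline.** Data collection and management continues: "baseline data will be collected from teachers shortly thereafter". Recruitment first states that participating families are randomised. It then sets out the teacher approach: an email to the principal, contact with the teacher, an information sheet with the signed consent form, and finally the request for baseline measures.
- **Blinding.** Concealment: "no attempt will be made to conceal treatment assignment from study team members, PCPs, behavioral health clinicians, and teachers".
- **Use of the score.** The Objective 1 analysis plan treats baseline as a modelled time point and reports the between-group difference in mean change. Determination of intervention effect sizes defines Cohen's d as that difference divided by the SD of the combined baseline scores. For teacher measures, the Objective 1 plan puts the emphasis on effect size.
- **Status.** Sample size calls the teacher analyses exploratory and expects about 100 evaluable cases.

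**The concern.** A baseline supports a change-score comparison because it precedes allocation, so that any difference between arms is due to chance. A score collected after the arm is known is a post-randomisation variable. It can already reflect what the rater expects, or early contact between family, clinician and school.

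This differs from unblinded outcome rating, which the article discloses as a pragmatic choice. A pragmatic design does not require a post-allocation score to serve as the baseline. The route is also plausible in this trial. PASS aims to build a working partnership between caregivers and teachers, and one teacher measure (the Parent-Teacher Involvement Questionnaire) rates that relationship. At stake are the teacher-report effect sizes, the only ones from an informant outside the family.

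**Working it through.** **Order of events.** The sections give this sequence:

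1. The consent visit, with parent and child baseline (Recruitment; Data collection and management).
2. Randomisation, and disclosure to the family at enrolment (Allocation concealment mechanism; Implementation).
3. A four-step teacher approach ending in the baseline request (Recruitment), which falls after consent (Data collection and management).

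No single sentence places step 3 after step 2, but every timing statement points that way, and the steps through the principal and teacher build in delay.

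**The plan's own figure.** Sample size claims 85% power at 0.30 SD for 240 parent- and child-report cases (300 × 0.8 = 240). It comes out close for a difference averaged over three time points with first-order autoregressive correlation 0.3:

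- Variance factor: (3 + 2(2 × 0.3 + 0.3²))/9 = 0.487.
- SE with 120 per arm: √0.487 × √(2/120) = 0.090 SD.
- Power at two-sided alpha 0.025: Φ(0.30/0.090 − 2.24) ≈ 86%.

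This figure does not cover teacher data, for which no power is claimed, so it is not the benchmark here.

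**Effect of a shifted baseline.** Estimate = (later PASS − later TAU) − (baseline PASS − baseline TAU). Let b be the between-arm shift in the baseline, positive if PASS children are rated better. Given the later scores, the estimate moves by −b. A positive b hides benefit and a negative b creates it. Were the teacher baseline a covariate instead, the move would be about −0.3b at correlation 0.3.

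**Size.** Inputs: about 100 teacher cases (Sample size), split 50 per arm (assumed from the 1:1 ratio); correlation 0.3 (stated in Sample size, assumed to apply to teacher ratings); alpha 0.05 (Objective 1 plan), taken as two-sided. The range of b is an assumption.

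- SE of the difference in change: √(2(1 − 0.3)) × √(2/50) = 1.183 × 0.2 = 0.237 SD.
- Effect detectable with 80% power: 0.237 × (1.960 + 0.842) = 0.66 SD.
- Type I error with no true effect: 1 − Φ(1.96 − b/SE) + Φ(−1.96 − b/SE).

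| Assumed shift b (SD, either direction) | b/SE | Move in estimate (SD) | Two-sided type I error |
|---|---|---|---|
| 0 | 0 | 0 | 5.0% |
| 0.05 | 0.21 | 0.05 | 5.5% |
| 0.10 | 0.42 | 0.10 | 7.1% |
| 0.20 | 0.85 | 0.20 | 13.5% |

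**The case against.** **The order is inferred, and teachers may not know the arm.** Both points stand. The time given for the teacher baseline is relative to consent, and the sequence in Recruitment could be narrative only. The listed teacher materials do not include the allocation, and only parents and children are named as being told. A rating soon after consent may also precede any PASS contact with the school. This limits the likely size of the shift, but nothing in the article prevents a rating made with knowledge of the arm.

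**The consequence is limited.** This stands too. Teacher outcomes are secondary, their analyses exploratory and underpowered, and a 0.10 SD shift is under half a standard error. But effect size is what these analyses are to be read by, and it is the quantity that moves.

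**Stronger readings.** A reader might infer that the parent baseline, and hence both primary outcomes, has the same defect, because no sentence requires the parent forms to be finished before the arm is shown. The documents do not support this. Parent baseline is taken at the consent visit and randomisation comes after consent. Medication status also shows that some parent baseline data come first, since it stratifies randomisation by parent-reported medication use at baseline. The exact gating step is a detail an article can leave to the full protocol, and the timeline table and flow figure are not available here. A reader might also set an assumed 0.10 SD shift against the 0.30 SD effect in Sample size, but that figure belongs to the parent- and child-report sample.

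**Conclusion.** The point holds for teacher-report measures only. As written, the plan allows teacher baselines to be collected after disclosure, apparently as the usual case, from raters to whom allocation is not concealed, and then uses them as the reference for change and for Cohen's d. Bias passes through one-for-one, with unknown size and direction. For an assumed shift of 0.05 to 0.20 SD, type I error is about 5.5% to 13.5%. This rests on about 50 children per arm, a correlation of 0.3 for teacher ratings, and a baseline shift that is not matched by an equal rating shift later, since a rating bias constant over time would cancel. No confirmatory conclusion depends on it, and no post-allocation score is shown for the primary outcomes.

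**What to change.** 1. Start teacher contact and send the teacher baseline form at consent, before disclosure where feasible. The principal and teacher contact steps mean that this will not always succeed.
2. Record the form's completion date relative to the date the arm was disclosed, and report by arm how many forms came after disclosure.
3. Keep the planned teacher analysis. Add a sensitivity analysis of the 16- and 32-week teacher scores that does not use post-disclosure teacher baselines and adjusts instead for pre-randomisation parent ratings and the stratification factors.

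Setting every post-disclosure form to missing in the main teacher analysis is not advised. It could remove most teacher baselines, and with them both the numerator and the denominator of the planned effect size.

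The cost is one date field and one extra analysis; the sample size does not change. The sensitivity analysis gives up some precision against a model adjusted for teacher baseline: at correlation 0.3 and 50 per arm, before any gain from parent ratings, the SE is √(2/50) = 0.200 SD against √(1 − 0.3²) × 0.2 = 0.191 SD. Against the change contrast (0.237 SD) it loses precision only if teacher ratings correlate above 0.5, the point at which 2(1 − r) falls below 1.
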